# Protocol for expanded indications of endoscopic submucosal dissection for early gastric cancer in China: a multicenter, ambispective, observational, open-cohort study

**DOI:** 10.1186/s12885-020-07312-3

**Published:** 2020-08-24

**Keywords:** Early gastric cancer, Expanded indications for ESD, Lymph node metastasis, Staging diagnosis scheme, Chinese population

## Abstract

**Background:**

The main treatment methods for early gastric cancer (EGC) include endoscopic submucosal dissection (ESD) and radical gastrectomy. However, appropriate treatment for patients who exceed the absolute indications for ESD remains unestablished. In China, evidence-based medicine for the expanding indications of ESD and accurate diagnostic staging for EGC patients are lacking. Thus, clinical studies involving Chinese patients with EGC are necessary to select appropriate treatment options and promote China’s expanded indications for ESD and diagnostic staging scheme.

**Methods:**

This is a multicenter, ambispective, observational, open-cohort study that is expected to enroll 554 patients with EGC. The study was launched in May 2018 and is scheduled to end in March 2022. All enrolled patients should meet the inclusion criteria. Case report forms and electronic data capture systems are used to obtain clinical data, which includes demographic information, results of perioperative blood- and auxiliary examinations, surgical information, results of postoperative pathology, and the outcomes of postoperative recovery and follow-up. Patients are followed up every 6 months after surgery for a minimum of 5 years. The primary endpoint is the rate of lymph node metastasis (LNM), whereas the secondary endpoints include the following: consistency, sensitivity, and specificity of the results of preoperative examinations and postoperative pathology; cut-off values for LNM; logistic regression model of expanded indications for ESD; and incidence of postoperative complications within the 30-day and 5-year relapse-free survival rates.

**Discussion:**

This study will explore and evaluate expanded indications for ESD that match the characteristics of the Chinese population in patients with EGC and will introduce a related staging procedure and examination scheme that is appropriate for China. Ethical approval was obtained from all participating centers. The findings are expected to be disseminated through publications or presentations and will facilitate clinical decision-making in EGC.

**Trial registration:**

The name of the registry is ChiCTR. It was registered on May 9, 2018, with the registration number (ChiCTR1800016084). The clinical trial was launched in May 2018 and will end in March 2022, with enrollment to be completed by December 2021. Trial status: Ongoing.

## Background

The improvement in public health awareness and the development of endoscopic technology have led to an increased detection rate and the overall incidence of early gastric cancer (EGC) [1, 2]. Statistics from the Chinese Association of Gastrointestinal Cancer Surgery show that EGC accounts for 19.5% of the overall gastric cancer cases in China [3]. Hence, scholars have begun to pay more attention to the early diagnosis and treatment of gastric cancer.

The current treatment methods for EGC mainly include endoscopic mucosal resection (EMR) or endoscopic submucosal dissection (ESD), and radical gastrectomy [4, 5]. However, the rate of lymph node metastasis (LNM) in early gastric cancer is low and, therefore, most patients undergo unnecessary or excessive lymph node dissection, which increases the surgical trauma [4]. Although EMR/ESD can be performed to completely remove the lesion, assessing the status of LNM around the stomach is currently impossible, resulting in incomplete treatment [6].

The absolute indications for ESD published in the updated Japanese gastric cancer treatment guidelines 2018 (5th edition) include the following: 1) differentiated intramucosal carcinoma with no ulcer and tumor size < 2 cm; 2) differentiated intramucosal carcinoma with no ulcer and tumor size > 2 cm; and 3) ulcerative, differentiated intramucosal carcinoma with tumor size < 3 cm that is accompanied by undifferentiated components [4]. However, controversy remains regarding the appropriate treatment for patients who exceed these absolute indications for ESD (i.e., expanded indications) [7–10]. Some studies found that ESD was suitable for some patients with EGC and expanded indications; these patients had better safety and effectiveness outcomes in the short-term after ESD [11]. Although the relative recurrence rate was increased in these patients, their long-term prognosis was better. Other studies recommend radical gastrectomy for patients with expanded indications because ESD may not meet the criteria for curative resection, and LNM may occur in the long-term [12, 13]. LNM is an independent risk factor for poor prognosis [14, 15]. Thus, a clinical trial, including patients with expanded indications for ESD, is necessary to select the treatment option that optimally balances radical tumor treatment and surgical trauma reduction.

Currently, evidence-based medicine in China supporting the use of expanded indications for ESD in patients with EGC is insufficient; hence, this multicenter, ambispective, observational, open-cohort study of Chinese patients with EGC is being conducted by the Beijing Friendship Hospital. The trial is expected to further refine the indications for ESD treatment in these patients.

## Methods/design

### Study aim

This study aims to explore and evaluate expanded indications for ESD that match the characteristics of the Chinese population in patients with EGC, and to introduce a staging procedure and examination scheme for EGC that is appropriate for China.

### Study design and setting

This is a multicenter, ambispective, observational, open-cohort study. The clinical trial was launched in May 2018 and will end in March 2022, with enrollment to be completed by December 2021. Between May 2018 and December 2022, patients from Beijing Friendship Hospital, Capital Medical University, Beijing Cancer Hospital, Peking University People’s Hospital, Peking University First Hospital, Chinese PLA General Hospital, and Cancer Hospital Chinese Academy of Medical Sciences will be selected for treatment. In total, 554 patients are expected to be included in the trial. After providing written informed consent, patients will undergo a D2 gastrectomy in a non-randomized, prospective study. For the retrospective study, researchers will recruit patients from January 2008 to April 2018, and all enrolled patients must meet the inclusion criteria. The detailed research process is described in Fig. 1. The latest protocol version is version 1.0 in April 2018.

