### Secondary endpoints

Accuracy, specificity, and sensitivity are evaluated using the following gold standards: postoperative histopathology of ultrasonic gastroscopy for tumor invasion depth, abdominal and pelvic enhanced computed tomography (CT) scan for LNM, pathological biopsy for tumor differentiation, and auxiliary examination for TNM staging.Cut-off values for LNM: A receiver operating characteristic curve is drawn for the clinical characteristics under different LNM rates to obtain the cut-off values.Logistic regression model: To explore the corresponding logistic regression model, postoperative histopathological examination for LNM, depth of infiltration, and degree of differentiation are evaluated in the univariate analysis. Variables with statistical significance in the univariate analysis are examined in the multivariate analysis.Complications: The incidence of postoperative complications within the last 30 days, including anastomotic fistula, pancreatic fistula, intestinal obstruction, delayed bleeding, and incision-related complications, are recorded. Postoperative complications classified as higher than Grade II, according to the Clavien–Dindo classification are regarded as clinically significant (Tables 2), [16].Five-year relapse-free survival rate: The time interval from the date of operation to the detection of tumor recurrence within 5 years is recorded.

**Table 2 Tab2:** Clavien–Dindo classification

Grade	Definition
I	Any complication that deviates from the natural course of the operation; treatments include antiemetic, antipyretic, analgesic, and diuretic drugs; infusion; physical therapy; as well as bedside debridement of incision infection.
II	Medications other than those permitted for grade I complications are required, including blood transfusion and total parenteral nutrition support.
III	Surgical and endoscopic interventions and radiotherapy are required.
IIIa	No general anesthesia is required.
IIIb	General anesthesia is needed.
IV	Life-threatening complications requiring intensive care.
IVa	Single-organ dysfunction
IVb	Multi-organ dysfunction
V	Death

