#### Follow-up

The postoperative follow-up is performed by a dedicated investigator. The patients are followed up every 6 months after discharge using outpatient visits, telephone, or mail. During the follow-up period, the patients undergo physical examinations, laboratory tests, a gastroscopy, a chest and abdominal CT scan, or an abdominal ultrasound assessment. The laboratory tests include routine blood examination, blood biochemistry, and tumor marker evaluation that includes CA19–9, CA125, AFP, CEA, and CA724. For patients that develop postoperative tumor recurrence or distant metastasis, a further detailed evaluation, including abdominal magnetic resonance imaging or PET/CT, will be performed to determine the feasibility of surgical resection. Each patient will be followed for at least 5 years or until a loss to follow-up. The detailed follow-up schedule is shown in Table 3.

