### Ethics and dissemination

This protocol has been reviewed and approved by the Ethics Committee of Beijing Friendship Hospital, Capital Medical University (2018-P2–015-02). The medical teams involved in this study have well-developed and standardized surgical techniques, and extensive experience, which reduces the potential risks associated with surgery and ensures the correct implementation of this study. In the event of complications, the medical teams have standardized measures to maximize the patient’s safety.

During the study, all personal data, such as name and sex, will be replaced with statistical codes or numbers and will be kept strictly confidential. All clinical data will be analyzed anonymously through the CRF and EDC systems to protect the privacy of the patients. Similarly, we plan to publish the results of this study in 2023 once all data have been obtained and evaluated. However, the article will not disclose any personal information.

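### The stated study end of March 2022 cannot be reconciled with at least 5 years of follow-up per patient and a 5-year relapse-free survival endpoint, and the two enrolment end dates conflict

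*Protocol article*

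**What the plan says.** The relevant statements in the protocol article are these.

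- **Study end and enrolment end.** Study design and setting: "The clinical trial was launched in May 2018 and will end in March 2022, with enrollment to be completed by December 2021". Trial registration repeats both dates, and the Abstract (Methods) repeats the study end: "The study was launched in May 2018 and is scheduled to end in March 2022".
- **A second enrolment window.** The next sentence of Study design and setting places selection of patients at the participating hospitals "Between May 2018 and December 2022".
- **Length of follow-up.** Follow-up: "Each patient will be followed for at least 5 years or until a loss to follow-up". Abstract: "Patients are followed up every 6 months after surgery for a minimum of 5 years". Table 3 has visit columns every 6 months out to 5 years.
- **Endpoint.** Secondary endpoints lists "Five-year relapse-free survival rate", timed from the operation.
- **Reporting.** Ethics and dissemination: "we plan to publish the results of this study in 2023 once all data have been obtained and evaluated".
- **Cohorts.** Determination of sample size gives 274 prospective and 280 retrospective patients. Study design and setting dates the retrospective patients from January 2008 to April 2018.

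No section describes follow-up after March 2022 or a separate, later analysis of survival.

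**The concern.** A 5-year endpoint needs 5 years between the operation and the data cut. The whole interval from launch to stated end is under 4 years. On the published calendar, then, neither the 5-year visits nor the follow-up commitment can be met for anyone in the prospective half.

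Two things are at stake. First, a pooled 5-year relapse-free survival figure in a 2023 report would rest, in its last year, wholly on retrospective patients. The Discussion itself describes earlier work in this field as mostly retrospective and open to bias, so the reader needs to know which cohort supports which part of the curve. Second, the sites have two dates on which enrolment might stop, one of them after the study is said to be over.

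**Working it through.** The check is calendar arithmetic: available follow-up = data cut minus operation date. I take the operation to fall in the month of enrolment. A later operation would only shorten the follow-up.

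**Prospective cohort at the stated end (March 2022)**
- First possible operation, May 2018: May 2018 to March 2022 = 46 months counted month to month, or about 47 months (3.9 years) from 1 May 2018 to 31 March 2022.
- Last enrolment, December 2021: December 2021 to March 2022 = 3 months, before the first 6-month visit in Table 3.
- Required: 60 months. The maximum available is about 47, so 0 of 274 reach 5 years.

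**When 5 years would be reached**
- First prospective patient: May 2018 + 60 months = May 2023, 14 months after the stated end.
- Last prospective patient: December 2021 + 60 months = December 2026, or December 2022 + 60 months = December 2027 under the other enrolment date.

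**Retrospective cohort at March 2022**
- March 2022 − 60 months = March 2017. Patients operated on by then can supply 5 years.
- Those operated on from about April 2017 to April 2018 cannot. That is 13 of the 124 months in the retrospective window (January 2008 to April 2018).

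**If follow-up ran past the stated end to the 2023 publication** (the article does not say that it does)
- January 2023: the earliest prospective patient has 56 months, so none reaches 60.
- December 2023: the earliest has 67 months. Only operations in May to December 2018 reach 60 months.
- Assuming uniform accrual over May 2018 to December 2021 (44 months): 8/44 = 18%, and 274 × 8/44 ≈ 50 patients. Over May 2018 to December 2022 (56 months) it would be 8/56 = 14%, and 274 × 8/56 ≈ 39 patients.

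**Horizons that March 2022 could support for the prospective cohort** (uniform accrual over 44 months)
- 3 years: operations by March 2019, so 11/44 = 25%, about 69 of 274.
- 2 years: operations by March 2020, so 23/44 = 52%, about 143 of 274.

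**Enrolment dates**
- December 2022 is 12 months after the other enrolment end (December 2021) and 9 months after the study end (March 2022).

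**The case against.** The strongest reply is that March 2022 may mark the end of a study phase and not the last follow-up contact. The Follow-up section makes the 5-year commitment without reference to that date, Table 3 schedules the visits, and this is a condensed article. That stands in part: the documents show conflicting dates, and a reader who infers that 5-year data will certainly go uncollected goes further than they allow. But the conflict is in what the article states, not in what it leaves out. March 2022 cannot simply mean the end of enrolment, because the same sentence gives enrolment its own date. Nothing provides for continuation, and publication in 2023 is tied to having all the data.

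A reader might also infer that the 5-year rate would come from retrospective patients only. That is too strong. Statistical analysis specifies Kaplan-Meier, so censored prospective patients stay in the risk sets up to about 46-47 months and contribute to the 5-year estimate. Only the stretch beyond that is purely retrospective. Nor does the article say that a single pooled 5-year curve will be presented.

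Finally, the affected endpoint is one of several secondary ones. The primary endpoint is determined by histopathology of the surgical specimen, and the sample size rests on it alone.

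**Conclusion.** The point holds as an internal contradiction of moderate weight, affecting one secondary endpoint and an explicit follow-up commitment. With March 2022 as the end, prospective follow-up runs from about 3 to 47 months, and no prospective patient reaches 5 years. The most recent part of the retrospective cohort falls short too.

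The word no rests on the March 2022 date alone. It would be tempting to say that the 2023 report also excludes every prospective patient. The dates do not support that: up to about 18% could reach 5 years by December 2023, given uniform accrual and follow-up past the stated end. What 2023 does rule out is complete 5-year data, which cannot exist before December 2026.

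The lymph node metastasis rate, diagnostic accuracy and 30-day complications do not depend on 5-year follow-up. The only bearing on them is that enrolment to December 2022 would outlast the stated study end.

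**What to change.** 1. Reconcile the two enrolment end dates, December 2021 and December 2022.
2. State two completion dates.
   - Surgery-time endpoints close after the last enrolled patient's operation and 30-day visit: early 2022 if enrolment ends in December 2021, early 2023 if it ends in December 2022.
   - Relapse-free survival closes when the last prospective patient reaches 5 years: December 2026 or December 2027 respectively.
3. Label any survival result in the 2023 report as interim, show it by cohort with numbers at risk, and give no 5-year rate for the prospective cohort.
4. If March 2022 must stand as the end of follow-up, restate prospective relapse-free survival at a horizon under 4 years, correct the 5-year follow-up statements, and report the 5-year rate for the retrospective cohort only.

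The cost is amended wording in the protocol and registration, and a later survival report. The visits are already in Table 3, so no new procedures are added. If resources were planned only to March 2022, however, the sponsor must provide for a further 57 months of follow-up (to December 2026) or 69 months (to December 2027).

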**Fig. 1 Fig1:**
[figure not shown]
Research process and flow chart

### Inclusion criteria

Patients aged 18–75 years (regardless of sex).Patients with Eastern Cooperative Oncology Group (ECOG) score ≤ 2 points and American Society of Anesthesiologists (ASA) score ≤ 2 points who can undergo a radical D2 gastrectomy.Patients without a history of gastrointestinal operation, chemotherapy, or radiotherapy.Patients with normal liver, kidney, heart, lung, and bone marrow function (GPT × 10^9^/L, PLT>10^9^/L).Patients who can understand and comply with the research protocol.Patients who can provide written informed consent by themselves or through their legal agent.Gastroscopic and pathologic diagnoses based on the following criteria: ①Tumor diameter > 30 mm, ulceration (UL)(+), and differentiated, mucosal carcinoma (T1a); ②Tumor diameter > 30 mm and differentiated, submucosal invasion depth < 500 μm (T1b SM1); ③Tumor diameter ≤ 30 mm and differentiated, submucosal carcinoma (T1b); ④Tumor diameter ≤ 20 mm, UL(−), and undifferentiated (T1a); ⑤Tumor diameter > 20 mm, UL(−), and undifferentiated (T1a); ⑥Tumor diameter ≤ 30 mm, UL(+), and undifferentiated (T1a); ⑦Tumor diameter > 30 mm, UL(+), and undifferentiated (T1a). The detailed inclusion criteria are shown in Table 1.

**Table 1 Tab1:** Inclusion criteria of expanded indications for ESD in patients with EGC

	T1a				T1b			
	UL (−)		UL (+)		SM1		SM2	
	≤20 mm	> 20 mm	≤30 mm	> 30 mm	≤30 mm	> 30 mm	≤30 mm	> 30 mm
**Differentiated**	ESD	ESD	ESD	EXPANDED	EXPANDED	EXPANDED	EXPANDED	SURGERY
**Undifferentiated**	EXPANDED	EXPANDED	EXPANDED	EXPANDED	SURGERY	SURGERY	SURGERY	SURGERY

ESD, ESD absolute indication; EXPANDED, ESD expanded indication; SURGERY, surgical indication for EGC; EGC, early gastric cancer; ESD, endoscopic submucosal dissection

### Exclusion criteria

Patients with a contraindication for gastroscopy.Patients with uncontrollable diseases, such as coagulation disorders, epilepsy, central nervous system diseases or mental disorders, cardiopulmonary insufficiency, unstable angina, myocardial infarction, a cerebrovascular accident that occurred within 6 months, and other surgical contraindications.Patients who cannot undergo general anesthesia or surgical treatment because of conditions related to other organs, or patients who are unwilling to undergo surgery.Patients with gastric stump cancer, recurrent gastric cancer, multiple primary malignant tumors in the abdominopelvic cavity, or a history of other malignant tumors within the previous 5 years.Patients who are pregnant or lactating.Patients who are participating in other clinical trials.

### Elimination criteria

A tumor with distant metastasis that is observed during the operation and postoperatively confirmed as advanced gastric cancer (pT_2_N_0_-_3_ M_0–1_) or non-gastric cancer by pathologic examination.Patients who do not follow the research plan and receive other anti-tumor treatments during the observation period.Patients with incomplete clinical data obtained after enrollment, which cannot be used in future statistical analysis.Patients who do not comply with the research protocol for treatment.Study termination as deemed necessary by researchers for the benefit of the patient.

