### Primary endpoint

The primary endpoint of this study is the rate of LNM. The scope of potential expanded indications for ESD is explored and evaluated based on the presence of LNM by histopathology and the positive rate of LNM with expanded indications for ESD.

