### Determination of sample size

The sample size was calculated by PASS 11.0 (NCSS Statistical and Data Analysis, USA) software and was estimated based on the preliminary research results of the Japanese clinical trial. According to previous studies with a single group design, the rate of LNM with expanded indications for ESD was 3% [20, 21] with an allowable error of 1.5%. Based on a one-sided test with an α value equal to 0.025, the estimated total sample size required for the trial is at least 497 patients. The withdrawal rate was assumed to be 20% during the follow-up. Therefore, the total sample size that is needed for this clinical study is approximately 554 patients, of which 274 and 280 are enrolled in a prospective- and retrospective study, respectively.

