## Discussion

The optimal treatment for EGC should balance radical tumor treatment and surgical trauma reduction. However, controversy remains surrounding how to choose an appropriate treatment in patients with EGC who exceed the absolute indications for ESD. The primary endpoint of this study is the rate of LNM. The scope of potential expanded indications for ESD will be explored and evaluated based on the presence of LNM by histopathology and the positive rate of LNM with expanded indications for ESD. The purpose of this study is to explore and evaluate expanded indications for ESD that match the characteristics of the Chinese population in patients with EGC and to introduce a staging diagnosis and examination scheme for EGC that is appropriate for China. To the best of our knowledge, this study is the first clinical trial to focus on Chinese patients with EGC, and the results could facilitate clinical decision-making.

Despite decades of research on the treatment of EGC, numerous problems remain unsolved. Regarding preoperative evaluation, Choi et al. showed that the overall accuracy of endoscopic ultrasonography in T staging of gastric cancer is 78% and only 72% in T1b submucosal staging. Thus, determining the depth of tumor submucosal infiltration remains difficult, which may result in unnecessary surgical trauma to some patients [22]. Similarly, Choi et al. reported that the tumor diameter measured under the endoscope was significantly smaller than that measured pathologically. Although the size deviation in 80% of tumor lesions was < 0.4 cm, the difference suggests that preoperative gastroscopy may underestimate the tumor diameter [23]. Consequently, ESD performed in patients with expanded indications may result in non-curative resection of the tumor and, thereby, affect the prognosis of patients.

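### Removing patients found to be pT2 after surgery deletes known understaging errors from the staging-accuracy endpoints, and understates the LNM rate if that rate is meant for patients as classified before treatment

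*Protocol article*

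**What the plan says.** Under Study design and setting, consent comes before surgery in the prospective part: "After providing written informed consent, patients will undergo a D2 gastrectomy in a non-randomized, prospective study". Under Inclusion criteria, entry rests on "Gastroscopic and pathologic diagnoses based on the following criteria"; the seven categories that follow are all T1a or T1b, as are all cells of Table 1.

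Under Elimination criteria, the first item removes "A tumor with distant metastasis that is observed during the operation and postoperatively confirmed as advanced gastric cancer", followed by a bracket giving pT2 N0–3 M0–1, or non-gastric cancer on pathology.

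Under Secondary endpoints: "Accuracy, specificity, and sensitivity are evaluated using the following gold standards: postoperative histopathology of ultrasonic gastroscopy for tumor invasion depth". The same item compares CT for LNM, biopsy for differentiation and the auxiliary examinations for TNM stage. The sentence is awkward, but the sensible reading is that postoperative histopathology is the reference standard.

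Under Primary endpoint, the target is "the positive rate of LNM with expanded indications for ESD", with LNM established by histopathology. The section does not say whether an expanded indication is the category assigned before surgery or the one confirmed on the specimen.

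The Discussion cites earlier work in which "the overall accuracy of endoscopic ultrasonography in T staging of gastric cancer is 78% and only 72% in T1b submucosal staging".

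**The concern.** The result of the reference standard decides who stays in the evaluation of the test. A prospective patient enters as T1. If the specimen shows pT2, the preoperative depth was wrong, and the elimination rule then takes that patient out. The errors removed are the largest understaging errors the study can observe, in a study that aims to introduce a staging and examination scheme for EGC and whose Discussion warns that imperfect preoperative assessment may lead to non-curative ESD.

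The same removal touches the primary endpoint. ESD is chosen before any gastrectomy specimen exists. At that moment a patient who is T1 on preoperative work-up but truly pT2 looks like an expanded-indication case. An LNM rate without such patients does not describe the group for whom that choice is made, although it can describe pathologically confirmed T1 disease.

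**Working it through.** **Inputs from the protocol.** LNM rate 3%, allowable error 1.5 points, one-sided α 0.025, 274 prospective and 280 retrospective patients (Determination of sample size); T-staging accuracy 78% (Discussion).

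**Assumptions, not in the protocol.** f, the share of enrolled patients found to be pT2 or deeper: 5% to 15% for accuracy, 5% and 10% for LNM. q, the LNM rate among them: 20% to 40%.

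**The plan's own figure.** n = z²p(1 − p)/d² = 1.96² × 0.03 × 0.97 / 0.015² = 496.8, so 497. This matches the protocol. The 3% and the 1.5-point error are thus the planned rate and half-width, and 1.5 points is a fair yardstick for a shift in the LNM rate.

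**Accuracy.** Every patient removed as pT2 was T1 at entry and so counts as incorrect. Removal leaves the number correct unchanged and shrinks the denominator:

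apparent accuracy = accuracy over all enrolled / (1 − f)

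| f | Prospective patients removed | 78% over all enrolled appears as | 78% among those retained means, over all enrolled |
|---|---|---|---|
| 5% | 274 × 0.05 ≈ 14 | 78/95 = 82.1% | 78 × 0.95 = 74.1% |
| 10% | 274 × 0.10 ≈ 27 | 78/90 = 86.7% | 78 × 0.90 = 70.2% |
| 15% | 274 × 0.15 ≈ 41 | 78/85 = 91.8% | 78 × 0.85 = 66.3% |

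The last two columns apply the same factor from either end. The direction needs no assumption; the size depends on f.

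**LNM rate over all preoperatively classified patients.** Rate = (1 − f) × 3% + f × q.

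| f | q = 20% | q = 40% | Excess over 3% |
|---|---|---|---|
| 5% | 2.85 + 1.0 = 3.85% | 2.85 + 2.0 = 4.85% | 0.85 to 1.85 points |
| 10% | 2.7 + 2.0 = 4.7% | 2.7 + 4.0 = 6.7% | 1.7 to 3.7 points |

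The excess is f × (q − 3%). It passes 1.5 points when q exceeds 3% + 1.5%/f, which is 33% at f = 5% and 18% at f = 10%.

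**Dilution.** These rates describe patients on whom the rule acts. If the shift applied to the prospective part alone, its effect on the pooled rate would be multiplied by about 274/554 = 0.49. The largest excess, 3.7 points, would become about 1.8, and the other three would fall below 1.5.

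**The case against.** - **The sentence appears to require distant metastasis.** Read literally, it does. But the bracket lists M0 and N0, which a rule confined to metastatic disease could not contain. Removal of pT2 without metastasis is the coherent reading, and the sentence needs repair in any case.

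- **A reader might infer that the LNM rate is biased outright.** The documents do not support that. Table 1 defines expanded indications only within T1, the endpoint rests on histopathology, and entry is on gastroscopic and pathologic diagnoses together. If the target is LNM in confirmed pT1 categories, leaving pT2 out is correct, and such a rate can still inform decisions once an ESD specimen has been examined. This objection stands for LNM; it does not reach the accuracy endpoints.

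- **A reader might also infer that accuracy for T1 against T2 becomes 100% by construction.** That goes too far. Data collection allows ultrasound or magnified gastroscopy, so a retained pT1 patient could have been overstaged on ultrasound. Discrimination within T1 (T1a, SM1, SM2), on which Table 1 turns, remains assessable.

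- **The size is not established.** True. The protocol gives neither f nor q, and its 78% comes from gastric cancer staging generally, not from patients preselected as T1. At f = 5% and q = 20% the LNM shift is 0.85 points, inside the allowable error.

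- **Just over half the sample is retrospective.** For those 280 patients pathology was already known and the basis of selection is unclear, so removal after enrolment acts clearly only on the 274 prospective patients.

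- **An analysis plan might define endpoint-specific sets.** It might, and it is not at hand. But elimination is a rule the protocol states, and the protocol describes no analysis that keeps these patients.

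**Conclusion.** The point holds for staging accuracy in the prospective part. Following the elimination rule can only raise apparent depth and TNM accuracy, by a factor of 1/(1 − f); at an assumed f of 5% to 15%, 78% would read as 82% to 92%.

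For the primary endpoint the conclusion is conditional. If LNM is meant for patients as classified before treatment, the rate is understated whenever LNM is more frequent in the removed patients than in those retained: 3% in place of 3.9% to 4.9% at f = 5%, or of 4.7% to 6.7% at f = 10%, with q assumed at 20% to 40%. If it is meant for confirmed pT1 categories, the removal is consistent with it. The defect there is that the protocol does not name the target. The protocol supports the direction of these effects, not their size.

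**What to change.** 1. Rewrite the first elimination item so that it is clear whether pT2 without metastasis is covered.
2. Do not remove prospectively enrolled, operated patients from the diagnostic-accuracy analyses because of their final pT stage.
3. State which LNM rate is the target, and report both: by preoperative category in all operated prospective patients, and by confirmed pT1 category. Give the number and nodal status of the pT2-or-deeper cases.
4. For retrospective patients, state whether selection used preoperative or pathological classification, and report them separately. Reselecting that cohort is not asked for; it would mean finding new records.

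**Cost.** Wording and one extra table. The patients have been operated on, so their pathology should already exist. Accuracy and LNM figures will look less favourable.

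**What it will not deliver.** With no clinical-T2 entrants, sensitivity and specificity for T1 against T2 remain limited. What becomes estimable is the share of clinical T1 that is truly pT1.
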